## Analysis Methods

### 27a. Statistical methods for each outcome and presentation of treatment effects.

“For comparisons between the study groups we will use Student’s t-test for continuous variables and in case of non-parametric data Kruskal-Wallis test. For comparisons of proportions, we will use Chi-squared tests. For the adjusted analyses we will use multiple linear and logistic regression analyses for continuous endpoints and proportions respectively.”[1]

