### 10. Randomisation

“Randomisation will be performed by a study nurse or a non-treating doctor using a randomisation program (dOxos CDS AB) on the day of the hCG trigger.

Randomisation will be performed 1:1:1:1. The randomisation program will take the following confounding factors into account; female age <37 or ≥37 years, number of previous oocyte retrievals, number of previous FET cycles, trial site and blastocyst Gardner score at the day of embryo freezing, to secure an equal distribution in the four study arms.”[1]

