## 11. Sample Size

“A total of 604 patients are required to have an 80% chance of detecting, at a significance level of 5%, an increase in live birth rate to 31% in the intervention group from 21% in the control group. Sample size calculation does not need correction for the two interventions, as they are considered fully independent of each other.”[1]

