## Section 4: Statistical Principles

### Confidence Intervals and P-Values

#### 16. Level of statistical significance to be used.

A significance level of 5% will be used.

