#### 17. Adjustment for Multiplicity

No adjustment for multiplicity will be conducted.

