### 27b. Adjustments for covariates.

The multivariable regression analyses will be adjusted for the stratification variables (trial site, female age <37 or ≥37 years, number of previous oocyte retrievals, number of previous FET cycles, blastocyst expansion grade at the day of embryo freezing) in addition to parity and day of blastocyst vitrification.[4]

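### Live birth gets both an unadjusted chi-squared test and an adjusted logistic analysis, and the SAP does not say which decides superiority; the unadjusted one is mildly conservative

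*SAP*

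**What the plan says.** Section 27a gives two routes to a result for a binary outcome such as live birth. The first is unadjusted: "For comparisons of proportions, we will use Chi-squared tests". The second follows directly: "For the adjusted analyses we will use multiple linear and logistic regression analyses for continuous endpoints and proportions respectively". The clarification beneath it says that the logistic results will be shown as adjusted risk differences. Section 18 plans 95% intervals for both the risk difference (RD) and the adjusted risk difference (aRD).

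On covariates, section 27b states: "The multivariable regression analyses will be adjusted for the stratification variables". It lists site, age group, previous retrievals, previous FET cycles and blastocyst expansion grade, and adds parity and day of vitrification. The reference it cites is, by its title, about improper analysis of trials randomised with stratified blocks or minimisation. Section 10 says that the randomisation program takes five factors into account "to secure an equal distribution in the four study arms". There the blastocyst factor is the Gardner score.

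Section 20 names a primary population (per-transfer) and section 26 a primary outcome (live birth). No section names a primary test or model. Section 27e dismisses sensitivity analyses as not relevant, so neither analysis is given a supporting role there. Section 16 says "A significance level of 5% will be used" and section 17 says "No adjustment for multiplicity will be conducted".

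**The concern.** There are two superiority comparisons (section 12) and two analyses of each. The per-transfer population alone therefore yields 2 × 2 = 4 live-birth results, and no rule says which two carry the conclusions. Choosing the deciding analysis before the data are seen is the task of section 27a.

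The choice also has a direction. When allocation is forced to balance on prognostic factors, the difference between arms varies less from trial to trial than it would under simple randomisation. A chi-squared test computes its variance as if allocation had been simple, so it overstates the uncertainty. The regression in section 27b takes the factors into account. At stake are a modest amount of power and, in a small share of trials, the verdict itself.

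**Working it through.** **1. Reproduce the planned sample size.** Section 11 plans 604 women for 80% power at the 5% level to detect an "increase in live birth rate to 31% in the intervention group from 21% in the control group". The pooled two-proportion formula, two-sided, gives per arm

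n = [1.960 × √(2 × 0.26 × 0.74) + 0.842 × √(0.21 × 0.79 + 0.31 × 0.69)]² / 0.10² = (1.216 + 0.519)² / 0.01 ≈ 301.

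That is 602 in total, against 604 stated. With 302 per side of each factorial comparison, power is 80.2%. The figure is reproduced, and it matches an unadjusted comparison of two proportions.

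**2. Size of the excess standard error.** If the balanced factors explain a share R² of the outcome variance, the unadjusted standard error (SE) is too large by the factor 1/√(1 − R²). Here R² = SD² / (0.26 × 0.74), where SD is the spread of individual live-birth risk due to those factors. The SAP gives no SD, so three values are assumed.

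- Weak: 0.054² / 0.1924 = 0.015, ratio 1.01
- Moderate: 0.104² / 0.1924 = 0.056, ratio 1.03
- Strong: 0.185² / 0.1924 = 0.178, ratio 1.10

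The true size of a nominal 5% unadjusted test is 2 × [1 − Φ(1.96 × ratio)], which is about 4.8%, 4.4% and 3.1%.

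**3. Simulation.** Inputs from the SAP: 604 women, four arms with equal allocation, five balancing factors, and 21% versus 31% (26% in both groups under the null). Inputs assumed: biased-coin minimisation (probability 0.8), eight sites, and the factor distributions and effects. The SAP names no allocation algorithm. The adjusted model held the five factors but not parity or day of vitrification, and its test was the Wald test of treatment. There were 2,500 null runs and 1,500 planned-effect runs per scenario.

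| | Weak | Moderate | Strong |
|---|---|---|---|
| Unadjusted SE / true SD, null | 1.01 | 1.02 | 1.09 |
| Type I error, unadjusted | 4.6% | 4.4% | 3.0% |
| Type I error, adjusted | 4.9% | 5.4% | 5.4% |
| Type I error, either may be claimed | 4.9% | 5.5% | 5.4% |
| Power, unadjusted | 81.2% | 80.5% | 83.1% |
| Power, adjusted | 81.8% | 82.1% | 88.1% |
| Opposite verdicts, null | 0.3% | 1.1% | 2.5% |
| Opposite verdicts, planned effect | 1.3% | 2.0% | 5.5% |

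The gain in power from adjustment is about 0.6, 1.6 and 5 points.

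**4. Precision.** The Monte Carlo standard error is √(0.05 × 0.95 / 2500) ≈ 0.4 points for type I error and √(0.8 × 0.2 / 1500) ≈ 1.0 point for each power. The two tests were run on the same data sets, so their difference is more precise than either figure. In the moderate planned-effect run the simulated SE ratio was 0.985, below the formula's value. An SD estimated from 1,500 runs carries an error of about 1/√3000 ≈ 1.8%, so the absolute powers in that column should be read loosely.

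**The case against.** The strongest reply is that the SAP already contains the right analysis. Section 27b adjusts for the stratification variables and cites a reference on this very problem, the clarification in 27a puts the result on the risk-difference scale, and section 18 gives it an interval. This stands. A reader might infer that the trial's intervals are too wide in general, but only the unadjusted RD and its interval are affected.

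Second, the error is in the safe direction and the planned power does not depend on adjustment. This also stands. A reader might infer that 604 is wrong or that the trial is underpowered. Neither follows, since 604 reproduces from an unadjusted test with 80.2% power. What is lost is a gain that could have been had.

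Third, a free choice between the two tests might be thought to inflate false positives. The runs do not show it. Claiming either result gave 4.9% to 5.5%, which these runs cannot reliably tell apart from 5%.

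Fourth, one could say that the ranking is obvious. It is not. The clarification suggests that the aRD leads. The order of 27a and the basis of the sample size suggest that the chi-squared test leads. A reader might therefore call the chi-squared test the primary test, but the SAP never labels it so. Both readings are reasonable, so this reply fails.

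**Conclusion.** The point holds in a limited form. The SAP plans two analyses of its primary outcome and does not say which one decides each superiority comparison. The unadjusted one ignores the five balancing factors and is mildly conservative: its standard error is about 1% to 10% too large and its simulated type I error 4.6% to 3.0%. Making the adjusted analysis decide would gain about 0.6 to 5 points of power. With the planned effect, the verdict would turn on the choice in 1.3% to 5.5% of trials.

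These sizes rest on assumed prognostic strength, an assumed allocation algorithm and an assumed number of sites. Two things do not rest on those assumptions: that the deciding analysis is open, which is read from the text, and the direction, which requires only that the balanced factors predict live birth.

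**What to change.** State in section 27a that, for each of Comparisons I and II in the per-transfer population, the primary analysis of live birth is the adjusted risk difference with its 95% interval and p-value, standardised from the logistic model in section 27b. State that the unadjusted RD and the chi-squared test are supportive.

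Reconcile the blastocyst covariate in the same revision. Section 10 balances on the Gardner score, while section 27b adjusts for expansion grade, only one part of that score, and calls it a stratification variable. The SAP should say which the randomisation program used and put that in the model.

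The cost is SAP wording only. The adjusted model and its interval are already planned, the covariates are already called for, and the sample size does not change. The revision should be dated before the outcome data are compared by arm.

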## Section 3: Study Methods

### 9. Trial Design

Randomised, single-blinded, controlled, trial using a 2 x 2 factorial design.

Participants will be randomised 1:1:1:1 to the following four study groups:

A) Luteal phase progesterone and warming+transfer 6 days after hCG trigger

B) Luteal phase progesterone and warming+transfer 7 days after hCG trigger

C) No luteal phase progesterone and warming+transfer 6 days after hCG trigger

D) No luteal phase progesterone and warming+transfer 7 days after hCG trigger.

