#### Clarification:

The results of from the logistic regression analyses will be presented as adjusted risk differences to better assess the clinical relevance of the potential treatment effects.

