#### **27d. Alternative methods if assumptions are violated.**

For comparisons of binary obstetric complications and perinatal outcomes, we will use Fisher's exact test, instead of the Chi-square test, if the number of events is ≤ 10.

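### The rare-event rule in SAP 27d changes only the unadjusted test, so the seven-covariate logistic model still applies to outcomes with 10 or fewer events, where it usually has no maximum-likelihood solution

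*SAP*

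**What the plan says.** - **Model (SAP 27a):** "For the adjusted analyses we will use multiple linear and logistic regression analyses for continuous endpoints and proportions respectively". No outcome is exempted.
- **Scale (clarification to 27a; section 18):** "The results of from the logistic regression analyses will be presented as adjusted risk differences". Section 18 requires a 95% confidence interval for adjusted risk differences but names no method for it.
- **Covariates (27b):** trial site, age group, number of previous retrievals, number of previous FET cycles and "blastocyst expansion grade at the day of embryo freezing) in addition to parity and day of blastocyst vitrification". That makes seven. The coding of the count and grade variables is not fixed.
- **Rare events (27d):** for binary obstetric and perinatal outcomes, "we will use Fisher's exact test, instead of the Chi-square test, if the number of events is ≤ 10". The adjusted model is not mentioned.
- **Safeguards (27c, 27e):** assumption checks and sensitivity analyses are both entered as not relevant.
- **Use (section 30):** congenital malformation and perinatal death are to be published with comparisons across study groups.

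**The concern.** 27d concedes that outcomes with 10 or fewer events need special handling, then applies this only to the test that needs it less. A chi-squared test on a sparse two-by-two table is approximate. A logistic model with more parameters than events will often be separated: some covariate pattern predicts the outcome perfectly, at least one coefficient runs to infinity, and no maximum-likelihood estimate exists. Software may still print an adjusted risk difference with an interval. The same table could then show a non-significant Fisher test beside an adjusted interval that excludes zero, and the SAP has no rule on which result leads. The outcomes exposed are the trial's harm data, such as perinatal death or very low birth weight. The SAP gives no expected counts, so their rarity is an assumption.

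**Working it through.** **1. The plan's own figure.** Section 11 plans for "an increase in live birth rate to 31% in the intervention group from 21% in the control group" with 80% power at the 5% level (two-sided assumed). With mean rate 0.26:

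n per arm = [1.96·√(2·0.26·0.74) + 0.84·√(0.31·0.69 + 0.21·0.79)]² / 0.10² ≈ 301, or 602 in total.

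This agrees with 604. Section 9 states: "Participants will be randomised 1:1:1:1 to the following four study groups", so each factorial comparison is 302 vs 302. Expected live births are 604 × 0.26 ≈ 157, rounded below to 160 (80 vs 80). Section 26c allows either women or a narrower population as the denominator, so both are shown.

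**2. Parameters against events.** Categorical coding uses three levels each for retrievals, FET cycles and expansion grade. The SAP's baseline tables list three categories for each.

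- 4 sites: intercept 1 + treatment 1 + site 3 + age 1 + retrievals 2 + FET cycles 2 + grade 2 + parity 1 + vitrification day 1 = 14.
- 8 sites: 14 + 4 = 18.
- Linear coding of the three variables saves 3 parameters, giving 11 and 15.

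Even at the ceiling of 10 events there is less than one event per parameter.

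**3. How often no maximum-likelihood estimate exists.** Events were placed at random with no treatment effect. The number of sites (2, 4 or 8) and the covariate distributions are assumptions.

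| Coding | Sites | 3–6 events | 10 events |
|---|---|---|---|
| Categorical | 2 to 8 | about 95–100% | about 60–99% |
| Linear | 8 | 96–100% | 96–97% |
| Linear | 4 | 85–100% (3–5 events) | about 27–35% |
| Linear | 2 | 88–91% at 3, 54–58% at 5 | 9% |

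Separation falls mostly on adjustment covariates, not on treatment. All events lie in one arm in about 20–28% of datasets at 3 events and almost never at 8–10. A standardised risk difference can therefore still be computed, but its interval is unreliable.

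**4. Would the analyst notice?** With categorical coding and 25 fitting iterations, the convergence flag was positive in 98–100% of datasets at N = 604. At N = 160 it was positive in 73–91% with 4 events and 97–100% with 6–10. Fitted probabilities fell below the threshold at which R warns of numerical 0 or 1 in 97–99% of datasets at 4 events, 81–91% at 6 and 28–55% at 10.

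**5. What the Wald interval does without covariates.** For a split of k events against 0 with m women per arm, z = √[k/(1 − k/m)].

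- 3–0, m = 80: z = √(3/0.9625) = 1.77, below 1.96, so it never excludes zero. Fisher p = 0.245.
- 4–0, m = 302: z = √(4/0.9868) = 2.01. It excludes zero at every 4–0 split, which has null probability 12.4% (12.0% at m = 80). Fisher p = 0.124 and 0.120.
- 6–0, m = 80: z = √(6/0.925) = 2.55, null probability 2.8%; a 5–1 split gives z = 1.68. Fisher also rejects only at 6–0 (p = 0.028).
- 10 events, m = 80: an 8–2 split gives z = 0.075/0.0378 = 1.98. The Wald interval excludes zero in 9.8% of cases and Fisher rejects in 1.8%.

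**6. The excess due to adjustment.** The adjusted risk difference is standardised, with an assumed delta-method 95% interval and categorical coding.

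| Births | Events | Adjusted interval excludes zero | Unadjusted Wald | Fisher |
|---|---|---|---|---|
| about 160 | 3 | 14–15% | 0% | 0% |
| about 160 | 6 | 10–12% | about 2–4% | about 2–4% |

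At 3 events and about 157 births, other assumed settings with 4 or 8 sites gave 13–20%. At N = 604 the excess over an unadjusted Wald interval was small, generally a few percentage points.

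**The case against.** **A large false-signal rate at 4 events.** A reader might infer that the adjusted model produces this, because its interval excludes zero in 11–12% of null datasets at N = 604 while Fisher never rejects. The comparison does not support that. A Wald interval with no covariates excludes zero in 12.4% of the same situations. At 10 events and 160 births the Wald interval again accounts for most of the conflict. This objection stands and confines the genuine excess mainly to the cells in step 6.

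**Failure would pass unseen.** This is also too strong. The convergence flag is often positive, but in the sparsest cases R, the planned software, would usually warn of fitted probabilities of 0 or 1. The warning is less dependable near 10 events.

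**The SAP never says in words that rare outcomes get the adjusted model.** True. It follows from 27a being written for all proportions and 27d altering only the unadjusted test. That is the natural reading, but it is an inference.

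**The figures rest on choices the SAP does not make.** Site number, coding, interval method and event counts are all assumed. With two sites, linear coding and 10 events, separation is uncommon (9%). A broad category such as any congenital malformation may well exceed 10 events.

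**Ectopic pregnancy.** It cannot be cited as a Fisher test beside a conflicting adjusted figure. The SAP lists it before the obstetric complications, so 27d does not reach it and no Fisher test is planned. As written, it would receive chi-squared and the same adjusted model.

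**Conclusion.** The point holds in limited form. Followed as written, the SAP applies a model of roughly 14–18 parameters to outcomes with at most 10 events, having accepted in 27d that such outcomes are too sparse for chi-squared. With categorical coding the model has no maximum-likelihood solution in nearly all datasets at 3–6 events and in most at 10. Materially misleading intervals, beyond what an unadjusted Wald interval would give, appear mainly with about 160 births at 3 events (14–15% against 0%) and 6 events (10–12% against 2–4%). The sizes depend on the assumed site number, covariate coding and distributions, a delta-method interval, and the outcomes actually being rare.

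The documents do not support extending this to the main result: with about 157 live births expected, the primary analysis is unaffected. This is a cheap improvement to the reporting of harms.

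**What to change.** Extend 27d with one sentence:

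*For any binary secondary outcome with 10 or fewer events in total, no fully adjusted logistic model will be fitted; the unadjusted risk difference with an exact or score 95% confidence interval and Fisher's exact test will be reported.*

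This also settles three smaller matters. It states that the threshold is a total, which 27d leaves open. It brings in rare reproductive outcomes such as ectopic pregnancy. By naming an exact or score interval, it removes the Wald-versus-Fisher conflict that exists even without covariates.

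The cost is one sentence and the loss of a covariate-adjusted estimate for these outcomes. If an adjusted figure is still wanted, a Firth-penalised logistic model with treatment and at most one or two covariates could be pre-specified. As an indication of feasibility, Firth fits with the full covariate set converged in 97–100% of simulated datasets.

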#### Clarification:

The results of from the logistic regression analyses will be presented as adjusted risk differences to better assess the clinical relevance of the potential treatment effects.

### 27b. Adjustments for covariates.

The multivariable regression analyses will be adjusted for the stratification variables (trial site, female age <37 or ≥37 years, number of previous oocyte retrievals, number of previous FET cycles, blastocyst expansion grade at the day of embryo freezing) in addition to parity and day of blastocyst vitrification.[4]

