## 20. Analysis Populations

Per-transfer (primary population): Women randomised, undergoing embryo transfer

Intention-to-treat: Women randomised.

As-treated: Women randomised, grouped according to treatment received.

Per-protocol: Women randomised, undergoing allocated treatment.

Women withdrawing consent to participate in the trial will be removed from all analyses.

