## 22. Eligibility

“Women fulfilling following criteria:

- Age 18-41 years
- Regular menstrual cycle (23-35 days)
- Planned to undergo single blastocyst transfer in a modified natural cycle with a high-quality (Gardner 3-6 A/B), vitrified blastocysts derived from 1.-3. IVF/ICSI cycle resulting in an embryo transfer on a public hospital.
- Giving informed consent

Exclusion criteria:

- Previous participation in the study
- Uterine malformations, intrauterine polyps or submucosal myomas
- Current breast feeding
- Receiving oocyte donation
- Preimplantation genetic testing for heritable diseases
- Blastocyst conceived with sperm from testicular sperm aspiration
- Active HIV or hepatitis B and C infection
- Known luteal phase insufficiency

Further exclusion criteria are the following contraindications to progesterone: allergy to the study medication, undiagnosed vaginal bleeding, current missed abortion or ectopic pregnancy, hepatic insufficiency or severe hepatic disease, history of genital or breast cancer, history of arterial or venous thromboembolism, thrombophlebitis or porphyria.”[1]

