## 25. Baseline Patient Characteristics

### 25a-b. List of baseline characteristics to be summarized and methods for summarizing baseline characteristics

| Baseline characteristics to be summarized | Unit                                                     | Method for summarizing baseline characteristics          |
|-------------------------------------------|----------------------------------------------------------|----------------------------------------------------------|
| Age                                       | Years                                                    | Means (SD) or median (IQR) depending on the distribution |
| Age ≥37 years                             | Years                                                    | n (%)                                                    |
| Age ≥35 years                             | Years                                                    | n (%)                                                    |
| Ethnicity                                 | Caucasian, African, Afro-Caribbean, Asian, Inuit, other. | n (%)                                                    |
| Civil status                              | Heterosexual, homosexual or single.                      | n (%)                                                    |

|                           |                                                                                                     |                                                          |
|---------------------------|-----------------------------------------------------------------------------------------------------|----------------------------------------------------------|
| Body mass index           | Kg/m                                                                                    | Means (SD) or median (IQR) depending on the distribution |
| Smoking daily             | Yes/no                                                                                              | n (%)                                                    |
| Menstrual cycle length    | Days                                                                                                | Means (SD) or median (IQR) depending on the distribution |
| Duration of infertility   | Years                                                                                               | Means (SD) or median (IQR) depending on the distribution |

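### Section 27b adjusts for age only as <37 or ≥37 years although age in years is collected; adding age in years would be a small, nearly free improvement

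*SAP*

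**What the plan says.** - **Adjusted models (SAP 27b).** The multivariable models are "adjusted for the stratification variables (trial site, female age <37 or ≥37 years" and the remaining balancing factors, "in addition to parity and day of blastocyst vitrification". Age appears in no other form.
- **Randomisation (SAP 10).** The program balances on "female age <37 or ≥37 years, number of previous oocyte retrievals, number of previous FET cycles, trial site" and on blastocyst score. The age term in 27b is thus the one used for allocation, and 27b cites a methods paper on the analysis of stratified and minimised trials.
- **Age as collected (SAP 25a-b).** The baseline table has a row for age in years, summarised as "Means (SD) or median (IQR) depending on the distribution". That wording recurs on many rows. What matters here is the row's unit, years, which shows that the continuous value is held.
- **Eligibility (SAP 22).** "Age 18-41 years".
- **Analysis sets (SAP 20).** The primary set is "Per-transfer (primary population): Women randomised, undergoing embryo transfer". Intention-to-treat takes all women randomised. The other two sets are "As-treated: Women randomised, grouped according to treatment received" and "Per-protocol: Women randomised, undergoing allocated treatment". Women who withdraw consent leave every set.

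**The concern.** A single cut at 37 gives the same fitted prognosis to every woman aged 18 to 36, which is 19 of the 24 eligible years of age (18 to 41). If live birth varies with age below 37, or between 37 and 41, the model cannot use that variation.

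Two things are at stake. In the randomised comparison it is precision only. In the as-treated and per-protocol sets, membership or grouping depends on what happened after randomisation, and the 27b covariates are the plan's only control of confounding. Section 27e plans no sensitivity analysis that would show an age imbalance left inside the bands.

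Section 27b already goes beyond the balancing factors by adding parity and day of vitrification. A further baseline prognostic covariate would therefore fit the plan's own approach.

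**Working it through.** **1. The plan's own figure.** SAP 11 gives 21% against 31%, 80% power, 5% significance and 604 women. With a two-sided test and pooled variance, p̄ = 0.26:

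n per arm = [1.960·√(2·0.26·0.74) + 0.842·√(0.21·0.79 + 0.31·0.69)]² / 0.10² = (1.216 + 0.519)² / 0.01 ≈ 301, so 602 in total against 604 stated. Power at 302 per margin is 80.2%. The figure reproduces, and nothing below changes it.

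**2. Information lost by the split.** The SAP gives neither an age distribution nor an age-outcome relation, so both are assumed: age truncated normal from 18 to below 42, mean 31 to 35, SD 3.5 to 5. With p the share aged ≥37, m₁ and m₀ the mean age effect in the two bands and v its variance:

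share kept = p(1−p)(m₁−m₀)² / v; share lost = 1 − share kept.

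| Assumed shape of the age effect | Share lost |
|---|---|
| Linear, all distributions | 46% to 80% |
| Linear, mean 33, SD 4.5 | 58% |
| Linear, mean 35 | 46% to 47% |
| Flat to 35, then declining | 18% to 24% |

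Check of the second row: the SD of age is 4.22 overall and 3.20 within bands, so the share lost is (3.20/4.22)² = 0.58.

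**3. Precision under randomisation.** Assumed: mean age 33, SD 4.5, live birth 21% and 31%, 302 per margin, 2,000 simulated trials, logistic model with standardised risk difference, age the only covariate.

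| Odds ratio per year | SE, <37/≥37 | SE, age in years | Reduction | Power |
|---|---|---|---|---|
| 0.95 | 0.03446 | 0.03429 | 0.5% | 81.1% → 81.4% |
| 0.92 | 0.03428 | 0.03394 | 1.0% | 80.7% → 81.1% |
| 0.90 | 0.03503 | 0.03467 | 1.0% | 81.1% → 82.0% |

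An approximate check by hand: one SD of chance imbalance within bands is 3.20·√(2/302) = 0.26 year. At 26% live birth, one year moves the risk by 0.26·0.74·|ln OR|, which is 0.99 points (OR 0.95) to 2.03 points (OR 0.90). The imbalance therefore contributes 0.26 to 0.53 points. Against an SE of about 3.5 points that is (0.26/3.5)² = 0.6% to (0.53/3.5)² = 2.3% of the variance, or roughly 0.3% to 1.2% of the SE. This agrees with the simulation.

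**4. Bias.** One million simulated women per case, true effect zero, Monte Carlo error about 0.1 point. Entries are points of live-birth risk difference, for odds ratios of 0.95, 0.92 and 0.90 per year.

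| Situation | Crude | <37/≥37 | Age in years |
|---|---|---|---|
| Group received depends on age, OR 1.02 per year (mean gap about 0.35 year) | −0.37, −0.47, −0.79 | −0.23, −0.25, −0.51 | −0.01, 0.07, −0.06 |
| Group received depends on age, OR 1.05 per year (mean gap about 0.9 year) | −0.95, −1.39, −1.67 | −0.60, −0.85, −1.01 | −0.07, 0.00, 0.06 |

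In the second case the two-level term leaves about 60% of the crude bias (for example 0.60/0.95 = 63%, 1.01/1.67 = 60%). When about 10% of one arm is excluded depending on age (OR 1.10 per year), the two codings differ by only 0.1 to 0.2 points. Under randomisation they agree within 0.02 points.

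**The case against.** The strongest reply is that nothing in 27b is wrong. It enters age exactly as the randomisation program does, cites a reference for doing so, and contradicts no other section. That stands: this is a refinement, not an error.

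Three stronger readings are tempting, and the SAP does not support them.

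- *Most of the prognostic information in age is thrown away.* This holds for many linear scenarios but fails at mean age 35, and it fails clearly if the effect is flat to 35. The SAP has no data to choose between them.
- *Age confounding remains in the non-randomised sets.* It can remain, but only if deviation or exclusion depends on age inside a band. For transfer day, section 19a names only clinic closing days and bank holidays, with no evident link to age. For progesterone, 19a and 19b speak of deviations in administration and of forgotten doses, which depend on patient behaviour. They neither show nor exclude a link to age. The per-transfer set is also defined by a post-randomisation event, and the SAP says nothing that ties failure to reach transfer to age and arm together.
- *Chance age imbalance biases the trial.* It does not. It is random error that the confidence interval already covers.

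A last objection is that a linear age term is itself an assumption and could burden models for rare outcomes. The first part is softened by keeping the indicator, which allows a step at 37. The second part is right: section 27d expects some obstetric and perinatal outcomes to have 10 events or fewer, and the term should not be forced there.

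**Conclusion.** A minor improvement. Coding age only as <37/≥37 gives up between about 18% and 80% of the information in age, on assumed distributions and shapes of effect. In the adjusted live-birth comparison this is worth about 1% of the standard error and less than 1 point of power, assuming odds ratios of 0.90 to 0.95 per year and no other covariate. Covariates correlated with age could make the gain smaller still.

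In the as-treated and per-protocol sets the possible residual bias is about 0.2 to 1.0 points in the scenarios where treatment received depends on age. That is small beside the 10-point target and a standard error of about 3.4 to 3.5 points. The intention-to-treat estimate is unbiased under either coding, and the sample size is unaffected.

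**What to change.** In 27b, add *female age in years (continuous)* to the covariate list and keep the <37/≥37 indicator as the balancing factor. Apply this to the adjusted models for live birth and the other reproductive outcomes, in all four analysis sets. State that the term is not required for outcomes with very few events; the limit of 10 events in section 27d could serve as the cut.

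The cost is one phrase and one extra model parameter, with no new data. The change should be dated before outcomes are compared by arm. If that has already happened, report the extended model as a labelled supplementary analysis so that it does not look data-driven.
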